### Participant timeline {13}

The period of enrolment will span a 24-month period, whereas patient participation will span a 6- to 12-month period that comprise of 4 visits for the CT-scan groups and 3 visits for the angiography group (Table 2).

**Table 2 Tab2:** Participant timeline

Timepoint	Enrolment	Allocation	CT-scan	CTO-PCI	Immediate follow-up	Close-out
	D0 −30 to 180 days ± 10 days	D0 −20 to 90 days ± 10 days	D0 −1 to 30 days	D0	D0 +2 to 4 days	D0 +180 days
Enrolment:	X					
Eligibility screen	X					
Informed consent	X					
Allocation		X				
CT scan			X			
Interventions:						
Comparator (wCT)			X	X		
Control (w/oCT)				X		
Assessment						
Demographic data	X					
Clinical data	X					
Risk factors	X					
Electrocardiogram	X					
Viability/ischemia test	X					
Coronary anatomy, EF and wall motion (echocardiogram or angiography)	X					
J-CTO scoring (angiography)	X					
Blood sampling	X				X	
ACT complications					X	
Adverse events	X				X	X
Symptoms, renal failure	X				X	X
MACE					X	X
TIMI flow	X				X	X

### Sample size {14}

A large registry-based study [4] on angiography-based CTO PCI revealed a procedural success rate of 87% (*n* = 3122). Two comparative studies [8, 9] on angiography-based CTO PCI versus CCTA-based CTO PCI reported success rates of respectively 90% (*n* = 30) vs. 63% (*n* = 43) and 93.5% (*n* = 187) vs. 84% (*n* = 168). Therefore, assuming a 90% success rate after 60 minutes wire manipulation in the CCTA-based CTO PCI group and 70% success rate after 60 minutes wire manipulation in the angiography-based CTO PCI group, an a priori sample size calculation revealed a minimum of 56 patients per group to detect a statistically significant difference of 20% with a power of 80% (*α* = 0.05). Assuming that <15% of patients will withdraw from the study, cross-over between groups, be lost to follow-up or have incomplete records, 65 patients will be included per group, amounting to a total of 130 patients to be included in the study.

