## Statistical methods

### Statistical methods for primary and secondary outcomes {20a}

Continuous variables will be reported as means, standard deviations, medians, and ranges, whereas categorical variables will be reported as numbers and proportions. Missing data will be considered separately for the calculation of proportions. Shapiro–Wilk tests will be used to assess the normality of data distributions. For normally distributed data, differences between groups will be evaluated using two-tailed *t*-tests. For non-normal distributions, differences between groups will be evaluated using Mann–Whitney *U* tests and Kruskal–Wallis tests. Effect sizes of differences between continuous variables (e.g. TIMI flow, procedure time, etc.) will be expressed using Cohen’s d, which can be interpreted as negligible (d<0.01),very small (0.01≤d<0.2), small (0.2≤d<0.50), medium (0.5≤d<0.80), large (0.8≤d<1.20), very large (1.2≤d<2.0), or huge (d≥2.0). For categorical data, differences between groups will be evaluated using chi-squared tests. All confidence intervals will be presented two-sided with a confidence level of 95%. Denominators used to calculate ratios for the intention-to-treat analysis will be the number of patients allocated to each treatment arm irrespective if they received the allocated treatment. Denominators used in the per-protocol analysis will be the number of patients that received treatment as allocated at enrolment. Denominators used in the as-treated analysis will be the number of patients that received treatment irrespective if the treatment was allocated at enrolment. Differences in success rate (successful wire crossing in ≤60 min with TIMI flow 3 is restored and residual stenosis is <30%) will be expressed in terms of absolute risk (as well as relative risk) to determine if procedures by CCTA CTO-PCA are 20% more successful compared to procedures by conventional Angiography CTO-PCI. Likewise, differences in complications between the two procedures will be expressed using absolute (as well as relative risk). A *p* value <0.05 will be deemed statistically significant. All statistical analyses will be performed using the latest version of R (R Foundation for Statistical Computing, Vienna, Austria).

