## Discussion

This randomised trial will provide insight into whether pre-procedural CCTA as opposed to conventional angiography for planning of CTO-PCI yield higher success rates of wire crossing in ≤60 min. Potential benefits of CCTA include shorter successful procedure times of CTO-PCI leading to less irradiation and contrast medium with lower complication rates.

This will be the second randomised controlled trial to investigate the impact of pre-procedural CCTA on CTO-PCI. Hong et al. [11] conducted a trial to test whether success rates of CTO-PCI increased when including pre-procedural CCTA as part of the treatment regimen, and found that including CCTA increased success rate (187(94%) versus 168(84%)), reduced MACEs (8(4%) vs. 10(5%)), but had higher cardiac-related deaths (1(0.5%) versus 0(0%)) and non-related cardiac deaths (2(1%) versus 0(0%)). Their study design did have some important flaws, which will be addressed in the present study. First, the previous trial enrolled any patient with CTO, whereas the present trial will only enrol patients with complex CTO (J-CTO≥2). The benefits of CCTA in addition to conventional angiography might be realised in more difficult cases of CTO. Moreover, the success of PCI in the previous study was less strict as suboptimal TIMI 2 flow was considered successful, whereas TIMI 3 flow will be considered successful in the present study. Second, the previous study, which was conducted at 12 centres, had a long inclusion period spanning 5 years and 9 months, whereas the present multi-centre study will have a 24-month inclusion period to reduce heterogeneity among patients, and with a higher inclusion rate to avoid potential selection bias. Third, the previous study relied on previous-generation CT scanning systems and protocols, whereas the present study will utilise current-generation equipment and protocols. Finally, the definition of the primary endpoint in the previous study compared success rates for any procedural time, whereas the present study will compare success rates only in cases where procedural time was <60 min.

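### The stated 56 patients per group give about 76–78%, not 80%, power for the planned two-sided chi-squared test, and the loss allowance counts cross-overs and withdrawals that the intention-to-treat analysis keeps

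*Protocol article*

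**What the plan says.** Sample size {14} assumes success within 60 minutes of 90% with CCTA planning ("assuming a 90% success rate after 60 minutes wire manipulation in the CCTA-based CTO PCI group") and 70% without ("70% success rate after 60 minutes wire manipulation in the angiography-based CTO PCI group"). From these it "revealed a minimum of 56 patients per group to detect a statistically significant difference of 20% with a power of 80" per cent, with alpha 0.05. Neither the test nor its sidedness is named there.

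The section then raises 56 to 65 per group, 130 in all: "Assuming that <15% of patients will withdraw from the study, cross-over between groups, be lost to follow-up or have incomplete records".

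Statistical methods {20a} compares categorical outcomes by chi-squared test, calls p < 0.05 significant, and adds that "All confidence intervals will be presented two-sided with a confidence level of 95" per cent. On the analysis sets it says: "Denominators used to calculate ratios for the intention-to-treat analysis will be the number of patients allocated to each treatment arm", whether or not the allocated treatment was received. The definition of that set under {18a} agrees: it keeps patients who cross over, have no CTO-PCI or have incomplete data. The primary endpoint is assessed in the intention-to-treat, per-protocol and as-treated sets, and none is named as primary.

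Two other sections bear on losses. Retention {18b} expects at most 5% missing data, because endpoints are collected during the procedure. Section {20c} calls the risk of non-adherence negligible.

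**The concern.** The size and the analysis do not match. A chi-squared test judged at p < 0.05 is non-directional, and the intervals are two-sided, but 56 per group is too few for 80% power on that basis. A reader would take a non-significant result as coming from a trial with 80% power at its stated minimum, which is not so.

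The second problem is how losses are treated. Dividing n by the fraction retained is right for patients who leave the analysis. Cross-overs, withdrawals and incomplete records do not leave the intention-to-treat denominator. They stay and shrink the difference between arms, and adding patients by head-count does not make up for that. The allowance fits the per-protocol set, not the intention-to-treat set.

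**Working it through.** **Inputs.** p1 = 0.90, p2 = 0.70, alpha 0.05, power 80%, 56 and 65 per group, losses below 15% (Sample size {14}); chi-squared test, two-sided intervals ({20a}); at most 5% missing ({18b}).

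**Reproducing 56.** Of the variants tried, only a one-sided test gives it. One-sided Fisher's exact test at 0.05 has power 79.4% at 55 and 80.25% at 56, so 56 is the first n to reach 80%. By enumeration, a one-sided Yates-corrected chi-squared test has the same power at these two sizes. One-sided formulas give 49 (uncorrected) and 58 (continuity-corrected).

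**Two-sided size.** With mean rate 0.80:

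- Pooled: n = [1.96·√(2·0.8·0.2) + 0.8416·√(0.09 + 0.21)]² / 0.2² = (1.1087 + 0.4610)² / 0.04 = 61.6, so 62 per group.
- Unpooled: n = 0.30·(1.96 + 0.8416)² / 0.04 = 58.9, so 59.
- Exact enumeration of Pearson's test: 79.7% at 58 and 80.5% at 59, so 59.
- Continuity-corrected formula: 72.

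**Two-sided power at 90% versus 70%.** The pooled formula is Φ[(0.2·√n − 1.1087)/√0.30]. At n = 56 the bracket is 0.708, at n = 65 it is 0.920.

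| Analysed per group | Pooled formula | Exact Pearson |
|---|---|---|
| 55 (65 × 0.85 = 55.25) | 75.3% | 77.2% |
| 56 (stated minimum) | 76.1% | 78.1% |
| 62 (65 × 0.95 = 61.75) | 80.3% | 81.0% |
| 65 (all enrolled) | 82.1% | 83.2% |

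The protocol does not say whether the chi-squared test is continuity-corrected. With the Yates correction, exact power is 69.4% at 56 and 77.5% at 65.

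**Intention-to-treat, all 65 per arm kept.** The protocol gives no rule for scoring patients without a result and no split of the 15%, so these three scenarios are assumptions. With affected fraction c:

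- Non-success in both arms: rates 0.9(1 − c) and 0.7(1 − c).
- Cross-over both ways: rates 0.9 − 0.2c and 0.7 + 0.2c.
- Cross-over from the CT arm only: rates 0.9 − 0.2c and 0.7.

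| Scenario (exact Pearson) | c = 5% | c = 15% |
|---|---|---|
| Non-success, both arms | 73% (85.5% vs 66.5%) | 56% (76.5% vs 59.5%) |
| Cross-over both ways | 74% (89% vs 71%) | 52% (87% vs 73%) |
| Cross-over, CT arm only | 78% (89% vs 70%) | 67% (87% vs 70%) |

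The pooled formula gives values up to about one point lower.

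**Cited studies.** The same paragraph announces angiography-based versus CCTA-based PCI and then lists 90% vs 63% and 93.5% vs 84%, which read literally favours angiography. It gives n = 187 and n = 168 for the second study. The Discussion reports the same two numbers as successes, in favour of CCTA. Arithmetic agrees: 187/0.935 = 200 and 168/0.84 = 200. The two sections cite different reference numbers, so that this is one study is inferred from the matching figures.

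**The case against.** The strongest reply is that the trial enrols 65 per arm, not 56. With full data that gives 82–83% two-sided power with the uncorrected test. If 5% are excluded, the protocol's own maximum for missing data, about 62 per arm remain, with 80–81%. This stands. A reader might infer that the enrolled 130 cannot deliver 80% power, and the documents do not support that.

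It is also fair that the allowance says less than 15%. Going from 65 to 56 is a loss of 9/65 = 13.8%, so 65 rather than 56/0.85 = 65.9, rounded up to 66, is at most one patient per arm. I make nothing of it.

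Intention-to-treat is not named as primary, so the conflict over cross-overs is with one of three sets. That limits the point but does not remove it, because the primary endpoint is to be assessed in that set.

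The one-sided Fisher origin of 56 is a reconstruction, since the section names no test. The mismatch does not depend on it: no two-sided variant tried gives 56. The errors in describing the cited studies do not enter the calculation, and the next sentence assigns 90% and 70% to the intended arms.

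**Conclusion.** The power stated for 56 per group is wrong for the planned test: 76–78% instead of 80%, a shortfall of 2 to 4 points, or 3 to 6 patients per arm. The enrolled 65 per arm cover this when losses are small, but not near the 15% ceiling, where about 55 per arm leave 75–77%.

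Separately, the allowance treats as removed patients whom the intention-to-treat set keeps. At 65 per arm, power there is about 73–74% if 5% count as non-success or cross over both ways, and 78% if 5% of the CT arm alone cross over. A reader might conclude that the trial has only about 50% power. The 52–67% range arises only if the whole 15% is a single kind of event under scoring that I assumed. The protocol states neither, so this is an extreme bound and not the plan's expected power.

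All figures rest on true rates of 90% and 70% and, unless noted, an uncorrected chi-squared test.

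**What to change.** Keep 130 patients and reword Sample size {14}:

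- State that the test is a two-sided chi-squared test at 0.05, without continuity correction if that is intended.
- Replace 56 by 62 per group (pooled formula), or by 59 if exact enumeration is the stated method.
- Restate power at 65 enrolled per group as about 82% with full data and 75–77% at 55 evaluable per arm.
- Take cross-over and non-receipt out of the attrition allowance. Treat them as dilution in the intention-to-treat analysis, and give the resulting power as a sensitivity range labelled with its scoring assumptions.
- As a minor correction, put the cited studies' arms in the right order and give group sizes in place of the success counts 187 and 168.

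The cost is one paragraph and a slightly less favourable power statement, with no extra patients.

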### Recruitment {15}

Patients compliant with inclusion and exclusion criteria will be invited to participate in the study. After patients are presented with the informed consent form, they will be given sufficient time to decide if they want to take part in the study.

## Assignment of interventions: allocation

### Sequence generation {16a}

An unstratified randomisation sequence will be generated before the commencement of the study by a software algorithm (IWRS, ClinInfo SAS, Lyon, France) and to be used in assigning patients to the CT group (A) or angiography group (B) in a 1:1 ratio. The randomisation list will consist of fixed block sizes of 4, e.g. AABB–BAAB–BABA–ABBA.

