### Trial design {8}

A randomised controlled open-label multi-centre trial in a superiority framework with 1:1 allocation ratio.

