### Who will take informed consent? {26a}

Participants in the study will sign the written informed consent which will be collected by the cardiologist (principal investigator) who will perform the CTO-PCI.

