### Intervention description {11a}

#### Preoperative assessment

The following assessments will be performed as part of the standard of care for the diagnosis of CTO:Conventional coronary angiographyIf symptoms and viability are not established through angiography, the patient will undergo one of the following:aStress electrocardiogram (ECG)bCardiac magnetic resonance imaging (MRI)cStress echocardiographydMyocardial scintigraphyCollection of biological markers: troponin, creatine kinase, creatinine, clearance of creatinine, haemoglobin. Preoperative angiography will be performed for all patients in ambulatory settings under local anaesthesia, with either a radial artery or femoral artery approach, with the former being the first choice if the artery is of good quality. An introducer sheath measuring 4 or 5 French (Fr.) is advanced within the artery using the Seldinger technique, and a catheter is advanced through the introducer up to the heart. A 6–8 cc iodine contrast injection in the coronary artery ostia allows visualisation of coronary artery anatomy under radiography. A picture registration is obtained and archived for planning of CTO-PCI. During the procedure heparin and nitrates are administrated.

If conventional angiography indicates a J-CTO score ≥2, the patient will be enrolled in the study, if they meet the eligibility criteria. Patients will then be randomly allocated to the CT group or angiography group. Patients in the CT group will undergo an additional CCTA scan (GE CT Revolution Scan 256; Iomeron 350 iodine contrast). The total dose length product (DLP, mGy/cm^2^) and computed tomography dose index (CTDI, mGy) will be recorded. Iodine contrast for the CCTA will be 55ml (10ml saline–55ml Iomeron 350–20ml saline at 5ml/s).

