### Concealment mechanism {16b}

The randomisation list generated in the IWRS software will be concealed from staff as well as patients. Only once the patient is included in the trial, will the treatment arm be assigned to the patient by the software, and reflected in the patient’s electronic case report form (eCRF) which is only accessible by the study staff. Patients will be blinded to their allocated group up to the point that they receive the treatment—patients will be aware of whether they receive CCTA before the CTO PCI.

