## Assignment of interventions: blinding

### Who will be blinded {17a}

This is an open-label study for the patient and treating cardiologist, but blinded for two cardiologists who will evaluate TIMI flow and residual stenosis after CTO-PCI.

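### Fixed, published blocks of 4 in an open-label trial weaken the promised allocation concealment, by an amount that depends on how recruitment is spread over centres

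*Protocol article*

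**What the plan says.** Trial design {8} describes the study as follows: "A randomised controlled open-label multi-centre trial in a superiority framework with 1:1 allocation ratio". Sequence generation {16a} provides for a single list ("An unstratified randomisation sequence will be generated before the commencement of the study by a software algorithm") and then fixes the block size and prints it with sample blocks: "The randomisation list will consist of fixed block sizes of 4, e.g. AABB–BAAB–BABA–ABBA".

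Concealment mechanism {16b} promises that "The randomisation list generated in the IWRS software will be concealed from staff as well as patients" and has the software release the arm only after inclusion. The arm then shows in the patient's "electronic case report form (eCRF) which is only accessible by the study staff". Implementation {16c} adds that the list number is shown there too.

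On who knows what, Who will be blinded {17a} says "This is an open-label study for the patient and treating cardiologist". Under {26a}, consent is "collected by the cardiologist (principal investigator) who will perform the CTO-PCI".

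On entry, Preoperative assessment ({11a}) says: "If conventional angiography indicates a J-CTO score ≥2, the patient will be enrolled in the study, if they meet the eligibility criteria". Table 2 also places J-CTO scoring at enrolment. However, Plans for assessment and collection of outcomes {18a} lists the angiographic anatomy used to calculate J-CTO among the items entered on the eCRF once the patient has been enrolled and allocated. No independent reading of the score before entry is described. The blinded cardiologists assess only TIMI flow and residual stenosis after the procedure.

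**The concern.** Hiding the list is not enough when its structure is known and past arms are visible. With every block fixed at 4, earlier arms within a block restrict the later ones. If numbering is consecutive, the list number in the eCRF also shows where a patient sits in a block.

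The person in a position to use this is the operator, who knows the arm of each treated patient and collects consent from the next. Eligibility turns on a cut at J-CTO 2, read from angiography. Some components, such as cap shape, calcification and bending, involve judgement. A lesion near the cut could in principle be entered now, deferred or scored differently according to the arm expected next.

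J-CTO grades procedural difficulty, and crossing within 60 minutes depends on difficulty. Selection of this kind would therefore act directly on the primary endpoint. The chi-squared comparison in {20a} does not adjust for it, and blinded reading of the result comes too late to prevent it.

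**Working it through.** The plan gives no figure for predictability, so there is none to reproduce.

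**Inputs.** Block size 4, 1:1, one unstratified list ({8}, {16a}); 130 patients ({14}). The share q of recruitment at one site is an assumption, because the number of centres is not given.

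**1. Observer who sees every allocation.** There are six possible blocks of two A and two B. The best guess is the arm with more places left in the block.

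- Place 1: correct 1/2, never certain.
- Place 2: correct 2/3, never certain.
- Place 3: the first two match with probability 1/3, and the arm is then certain; otherwise it is even. Correct 1/3 + (2/3)(1/2) = 2/3.
- Place 4: always certain.

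Certain: (1/3 + 1)/4 = 33.3%, or about 43 of 130 patients. Correct: (1/2 + 2/3 + 2/3 + 1)/4 = 2.833/4 = 70.8%.

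**2. Operator who sees only one site.** Let each earlier patient in the block belong to that site with probability q, and assume that the operator knows which block the next patient falls in. That is generous, so the results are upper bounds.

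Certainty requires having seen two patients on the same arm:

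- Place 3: q²/3.
- Place 4: q³ + 3q²(1−q)/3 = q².
- Average over the four places: (q²/3 + q²)/4 = q²/3.

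Probability of a correct best guess:

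- Place 1: 1/2.
- Place 2: 1/2 + q/6.
- Place 3: 2/3 − (1−q)²/6.
- Place 4: 2/3 − (1−q)³/6 + q³/3.

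At q = 0.5 this is (0.500 + 0.583 + 0.625 + 0.688)/4 = 59.9%, and certainty is 0.25/3 = 8.3%.

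| Assumed share q | Certain | Best guess correct |
|---|---|---|
| 100% | 33.3% | 70.8% |
| 75% | 18.8% | 64.6% |
| 50% | 8.3% | 59.9% |
| 20% | 1.3% | 54.4% |

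Simulation gives the same values. Without any use of list numbers, simply guessing the opposite of the site's last arm is right 58.8% of the time with two equal centres and 54.3% with five (simulated).

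**3. Randomly varying blocks of 4, 6 and 8.** For an observer who sees every allocation and updates over the possible sizes, simulation gives about 2% certain and about 68% guessed correctly. Nearly all certainty goes, but the best guess falls by only about 3 points from 70.8%.

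**The case against.** The strongest reply is that the design already limits prediction. There is one list for all centres, held in an IWRS and hidden from staff, and the arm is released only after inclusion. Confidentiality {27} places data collection with staff at each site, and nothing says that one centre sees another's allocations. This stands: the 33% and 71% are upper limits, and for a site with a fifth of recruitment almost no assignment is certain. It does not remove the point, because the article does not exclude a dominant centre or shared visibility.

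Secondly, steering at the cut should show as an excess of J-CTO 2 in one arm. The score is recorded for everyone, and {20b} splits patients into J-CTO 2 and ≥3. That is a partial safeguard, but it relies on the score having been recorded before the arm was known, which {18a} leaves open.

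A reader might infer that operators can foresee a third of assignments and will steer patients. The documents show neither. A reader might also put the bias at 3 points, from two patients in an arm of 65 (2/65 = 3.1%). That assumes both the number steered and that every one of them changes from failure to success or the reverse. Neither assumption has support in the article.

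**Conclusion.** The weakness is real and moderate. A fixed, disclosed block size, an unblinded operator who collects consent, and an eligibility score not clearly recorded before allocation together undercut the concealment stated in {16b}.

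For an operator confined to one site, certain prediction runs from about 19% at a 75% share of recruitment to about 1% at 20%, with best guesses of about 65% down to 54%. The full 33% and 71% apply only if one centre enrols nearly everyone or staff can see all allocations. The shares are assumptions, and the single-site figures are upper bounds because they credit the operator with knowing which block comes next. No size can be given for any resulting bias in the 60-minute success rates. The case for change rests on a low cost against a risk that the design leaves open.

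**What to change.** For assignments not yet made:

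1. Have the IWRS generate the rest of the list with randomly varying block sizes, for example 4, 6 and 8. Withhold the sizes from sites, start at a block boundary, and replace the fixed-size sentence in {16a}.
2. Require the angiographic J-CTO score and its items to be locked in the eCRF before the arm is released, and align {18a} with this.

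Both parts are needed, and together they still leave a gap. Varying the blocks removes nearly all certain prediction but leaves best-guess accuracy at about 68% for an observer of every allocation. The lock prevents re-scoring once the arm is known, but not deferral of a patient.

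The cost is a regenerated list remainder and one eCRF rule. An amendment with a favourable ethics committee opinion may also be needed under {25}, since the allocation method plausibly bears on validity. End-of-trial imbalance could reach 4 patients (half of a block of 8) instead of 2; a switch in mid-block could add a further 2, hence the block boundary. The trial started on 1 May 2022 with 24 months of enrolment planned, so how many assignments remain is not known from the article.
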